#### Eligibility

##### Inclusion

- Patients who received an ICD for the first time, and who prior to hospital discharge agreed to participate in the entire programme.

- Patients with physician permission prior to randomization to participate in the physical training programme.

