### Randomisation

Before randomisation baseline data were collected. Patients were randomised while in hospital.

The enrolling research assistant or primary investigator called for randomization allocation. Randomisation (block of 4) was done by voice-respondent in a 1:1 ratio to intervention group or control group (standard care) and there was stratification according to gender and left ventricular ejection fraction (below or above 35%).

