### Outcomes

Using questionnaires, interviews, exercise-tests, a 6-minute walk test (6-MWT), interrogation of the ICD and register-based follow-up, the effect and meaning of the programme are evaluated (Table 2). The pre-training exercise test is performed at 3 months and therefore not reported here.

**Table 2 T2:** Outcome Measures

Measurement	Time
**SF-36**	Baseline, 3-6-12 month

QLI-C	Baseline, 3-6-12 month

IDAS	Baseline, 3-6-12 month

Sex after ICD survey	6 month

ICD and Avoidance Survey	6-12 month

SCA knowledge assessment	Baseline, 12 month

**Exercise test**, 6MWT	3-6 month

ICD interrogation	3-6-12 month

Work	12 month

Rehabilitation elsewhere	12 month

Qualitative interview	12 month

Registry data	2 years

SF-36 and exercise test are primary outcome measures.

Primary outcome measures: Due to the nature of rehabilitation, including both physical and psychological components, the two primary outcome measures are perceived health measured by the Short Form-36 [33,34] questionnaire and Peak VO2, measured by a standardized protocol according to guidelines [35]. The test is performed on bicycle ergometer with an initial workload of 12.5 W and increased 12.5 w every minute until exhaustion or at 5 beats/min heart rate below ICD activation threshold. No gas analyses are conducted.

Secondary outcome measures: Physical capability is measured by an exercise test combined with the six minutes walk tests which have been proved to be effective measures of functional capacity in patients performing cardiac rehabilitation [30,36,37]. Further, exercise training data consist of the number of sessions, duration and heart rate.

Ventricular arrhythmia: 1. ICD-shock 2. Anti-tachycardia pacing is registered by interrogation of the ICD.

Questionnaires: Quality of life is measured by Quality of Life Index-Cardiac version (QLI-C) [38], knowledge of the ICD by Sudden Cardiac Death (SCD) knowledge assessment [20], ICD-adaptation using Implanted Devices Adjustment Scale (IDAS) [39], sexual problems or dysfunction by the Sex After ICD Survey [40] and avoidance behaviour is measured by ICD and Avoidance Survey [40].

Ancillary questions developed for this study: amount of participation in rehabilitation outside the project, and work status/sick leave before and after ICD implantation.

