### Statistical methods

The statistical analyses of the effects of rehabilitation are conducted based on a predefined statistical protocol using SPSS 17.0 for Windows. The analysis will adopt an analytical approach on all available data, meaning that all data obtained are included in analyses, regardless of adherence to the study protocol. Only data from patients following through the program will be included in the analysis of the endpoints. Accordingly, there is no imputation of missing data. Questionnaire responses will be converted to numerical scores using standard methodologies. Continuous data are checked for normality of distribution, and log-transformed if required. The baseline characteristics will be presented by group to present similarities across treatment, but according to recommendations no significant testing will be performed [43]. The socio-demographic and clinical characteristics of individuals who drop out from the study will be compared with those who completed the study and drop-out characteristics between groups will be compared. The effectiveness of the intervention will be examined using blinded analysis of variance. The primary comparisons will be Two independent samples T-test for the mean difference between two independent samples. Paired T-tests of equality of means will be used for within group analysis of difference over time. Further, univariable and multivariable regression analysis will also be used to investigate the effect of the intervention on the endpoints. The type of regression analysis will depend on the endpoint in question. Demographic, clinical and questionnaire data will be included in multivariable analysis in order to control for their potential confounding effects. The level of significance is set at p < 0.05. Data will, for continues data, be shown as means ± standard deviation or percentage. Categorical data will be shown as percent. Twelve month follow-up data and results obtained from Danish registries regarding hospitalisations are used for follow-up comparison. Due to the skewed distribution of length of hospital stay and repeated measurements of hospital admissions on patients these register-based tertiary outcomes will be analyzed using multivariate random-effect modelling with patients as random effects. Further analysis will be conducted using the Cox regression model including time to first event as outcome variable. At baseline 46% (n = 91) of the population was employed. This is a rather small number of patients and sickness absence will be included as a measure when evaluating employment status. The direct costs of healthcare are calculated by a retrospective top-down method [44]. All other costs are extracted from relevant registers.

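### Within-arm paired t-tests are planned for change over time with no limit on interpretation; they cannot separate the programme from recovery and should be descriptive only, with conclusions resting on the between-arm difference.

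*Protocol article*

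**What the plan says.** The statistical methods section of the protocol article introduces its analyses by their purpose: "The statistical analyses of the effects of rehabilitation are conducted based on a predefined statistical protocol using SPSS 17.0 for Windows". It names an analysis of variance for effectiveness, then the primary test: "The primary comparisons will be Two independent samples T-test for the mean difference between two independent samples". The next sentence is "Paired T-tests of equality of means will be used for within group analysis of difference over time". Univariable and multivariable regression on the intervention effect follow. One 5% significance level is set for all of this. No sentence says that the paired tests are descriptive, or that they carry no weight in judging the programme.

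Table 2 lists SF-36 (co-primary), QLI-C and IDAS at "Baseline, 3-6-12 month". On timing, the randomisation section says "Before randomisation baseline data were collected. Patients were randomised while in hospital", and the inclusion criteria describe "Patients who received an ICD for the first time, and who prior to hospital discharge agreed to participate in the entire programme". Read together, the questionnaire baseline was taken in hospital after the device was implanted. The exercise test behind the other primary outcome has no in-hospital value: it is first done at 3 months, before training, and repeated at 6 months.

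**The concern.** A paired test inside one arm asks whether that arm changed. The trial was randomised to ask whether the arms changed differently. From an in-hospital baseline after implantation, both arms may well improve on health questionnaires without any programme, through recovery and regression to the mean. The article itself treats the early period as unsettled, since it delays training by three months for reasons of stability. In the control arm the paired test measures this background change. In the intervention arm it measures background change and programme effect together and cannot split them. The exercise test avoids the in-hospital baseline, but its change from 3 to 6 months within one arm still confounds the programme with time.

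What is at stake is how the results are read. If the intervention arm shows a significant improvement and the control arm does not, that pattern looks like evidence for the programme, yet it is not a test of the difference between arms.

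**Working it through.** **Inputs.** From the sample size section: General Health (GH) SD 22, expected effect 10 points, 5% level, 80% power, 154 patients needed, 196 included to allow for 20% drop-out. Assumed, because the article gives no figure: two-sided testing, zero programme effect, the same true recovery *m* in both arms, and a baseline-to-follow-up correlation *r* of 0.3 to 0.7.

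**Step 1: the plan's own figure.** Per arm, 2 × (1.960 + 0.842)² × 22² / 10² ≈ 76, or 152 in total. The exact t-test calculation gives 77 per arm, or 154, as stated. Allowing for drop-out, 154 / 0.8 = 192.5, so 193 against the stated 196. The planning inputs are therefore read correctly. Patients expected at follow-up: 196 × 0.8 / 2 = 78.4, so 78 per arm.

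**Step 2: the paired test with no programme effect.** SD of change = 22 × √(2(1 − r)). At r = 0.5 this is 22, and the standard error is 22 / √78 = 2.49. For m = 5 the noncentrality is 5 / 2.49 = 2.01. The noncentral t distribution with 77 degrees of freedom gives a probability *p* of significant improvement of 0.51.

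**Step 3: significant in the intervention arm only.** The arms are independent with the same *p*, so this probability is p(1 − p). It cannot exceed 0.25, which is reached at p = 0.5.

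Results at r = 0.5, with the between-arm t-test on change scores from 20,000 simulated trials:

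| Shared recovery (GH points) | Intervention arm significant | Intervention arm only | Between-arm test significant |
|---|---|---|---|
| 0 | 2.5% | 2.4% | 4.9% |
| 3 | 22% | 17% | 4.8% |
| 5 | 51% | 25% | 4.8% |
| 10 | 98% | 2% | 4.8% |

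**Step 4: sensitivity to the correlation, at 5 points.**
- r = 0.3: SD of change 26.0; intervention arm significant in 39%, that arm only in 24%.
- r = 0.7: SD of change 17.0; intervention arm significant in 73%, that arm only in 20%.

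**The case against.** The strongest reply is that the trial does not depend on these tests. The primary comparison is a two-sample t-test between arms, supported by analysis of variance and regression. All of these cover the questionnaire endpoints, and the between-arm test keeps its 5% level whatever recovery the arms share. The article does not say that efficacy will be concluded from within-arm p-values, and its discussion promises caution over multiple comparisons. It also refers to a predefined statistical protocol that is not shown and may set out how the four visits are used. All of this stands, and it sets the priority. It leaves one gap: the paired tests carry the same significance level with no limit on interpretation, and a general caution about multiplicity does not address confounding with time.

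The baseline data do not settle how much recovery to expect. Role Physical is low (39.1 control, 36.6 intervention), but GH is 59.5 and 58.7, close to the planning value of 60. The recovery figures above are therefore assumptions and not estimates.

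Some stronger readings are tempting but not supported:
- A reader might infer that paired tests are the only analysis of the repeated measures. They are only the sole method named specifically for change over time.
- A reader might infer that the in-hospital baseline affects every outcome. It does not apply to the exercise test.
- A reader might quote 50% (2 × 25%) as the rate of misleading trials at 5 points. Half of those show improvement in the control arm alone, which would not suggest benefit. Nor does significance in both arms point to a programme-specific effect.

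**Conclusion.** The point holds as a weakness of a supplementary analysis. The within-arm tests cannot separate the programme from recovery, regression to the mean or time. With no programme effect and a shared 5-point GH recovery, the intervention-arm test would be significant in about 51% of trials (39% to 73% across correlations 0.3 to 0.7). The misleading pattern of significance in that arm alone would occur in about 25%, which is its ceiling. These figures rest on the planning SD, 78 per arm, and assumed values for recovery and correlation.

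A reader might go further and conclude that the trial's efficacy inference is compromised, or that the paired tests measure recovery instead of the programme. The document supports neither: the primary inference is between arms and unaffected, and in the intervention arm the paired test captures both components together. Priority is low to moderate.

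**What to change.** 1. Present within-arm changes descriptively (means with confidence intervals), without hypothesis tests, and state that conclusions about the programme rest on the between-arm difference.
2. For SF-36, QLI-C and IDAS, analyse change over time with one linear mixed model per outcome: arm, visit, arm-by-visit interaction, baseline score, and the two stratification factors (gender and left ventricular ejection fraction group). Report the between-arm difference with its 95% confidence interval at 3, 6 and 12 months.
3. For the exercise test, which has no value before randomisation, report the between-arm comparison and treat the 3-to-6-month change within each arm as description only.

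The first and third changes remove the problem by wording alone. The second also uses the four visits for the randomised question and gains precision from the baseline score. At a single visit the residual variance relative to an unadjusted comparison of follow-up scores is 1 − r², which is 1 − 0.25 = 0.75 at the assumed correlation of 0.5. The cost is analysis-plan text and a standard model. Random-effect modelling is already planned for the registry outcomes, and no new data or patients are needed.

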
### Ethical considerations

The study is approved by the regional Ethics Committee (j.nr. H-B-2007-014), National Agency for Data Security (j.nr. 2007-41-0932) and registered at ClinicalTrials.gov (ID: NCT00569478). Patients were asked to participate in the study after receiving oral and written information, and were given time to reflect on their participation in the study before giving written informed consent. All data are treated in confidence and patients are assured anonymity. The study follows the recommendations of the Declaration of Helsinki II [45].

### Safety

No risks are anticipated during the psycho-educational consultations.

Studies have shown that it was safe for patients with ICDs to participate in physical training [13,16,27]. This intervention is not aimed at maximum performance, but is a recreational programme. A "cool down" period was incorporated in exercise and testing, which has previously resulted in 45,000 exercise tests without complications over a 10 year period [46].

### Participants recruitment and flow

During the inclusion period October 2007-November 2009, 610 patients had ICD implantation at the hospital (Figure 3). Due to local policies patients were not asked to participate if they were eligible for or included in pharmaceutical trials. Not meeting the inclusion criteria was due to other somatic diseases (n = 49), psychiatric disease or cognitive dysfunction (n = 20) and language (n = 11). A total of 196 patients were included.

**Figure 3 F3:**
[figure not shown]
**Flowchart of Patients Included in COPE-ICD**.

### Baseline measures

Most participants are men (79%) and the mean age was 58 (SD 13.2), range 20-85. The mean LVEF is 32 (SD17.5) and most (46%) are NYHA class 2 and 64% received the ICD for primary prevention (Table 3). The medication status at baseline is presented in Table 4. The mean walk capacity measured by 6MWT is 417 m., Table 5. The perception of health measured by SF-36 is 42.6 for physical component scale (PCS) and 47.1 for mental component scale (MCS), a higher score indicating better perception of health, scale range 0-100 (Table 6). Quality of life score is 26.4 (Table 6), scale range from 0-36, a higher score indicating better quality of life. Baseline knowledge of the ICD score is 20 (Table 6), scale range 0-25.

**Table 3 T3:** Demographic and Physical Profile

	Control gr. n (%)	Intervention gr. n (%)
Male gender	76 (78)	79 (80)

Age (mean)	58	58

Employed	50 (52)	41 (42)

Primary prophylactic indication	67 (69)	63 (64)

VF prior to ICD implantation	20 (20)	21 (21)

LVEF (mean/SD) 73% of tot pop ≤ 35	32.7 (18)	32.2 (17)

NYHA I	18 (19)	30 (31)

NYHA II	44 (46)	42 (43)

NYHA III	32 (33)	24 (25)

NYHA IV	1(1)	2 (2)

BMI ≥ 30	19 (20)	24 (24)

Atial fibrillation	21 (22)	27 (27)

CRT device	9 (9)	14 (14)

History of IHD	57 (59)	45 (46)

Previous MI	33 (34)	20 (21)

Previous PCI	29 (30)	28 (29)

Previous CABG	21 (22)	14 (15)

History of HF	73 (75)	76 (78)

Diabetes	10 (10)	12 (12)

Hypertension	23 (24)	18 (18)

COLD	1 (1)	2 (2)

Other chronic disease	24 (25)	27 (28)

CRT: Coronary resync. therapy. IHD: Ischemic heart disease. MI: Myocardial infarction. PCI: Percutaniuos catheter intervention. CABG: Coronary artery bypass graft. HF: Heart failure. COLD: Chronic Obstructive Lung Disease.

**Table 4 T4:** Baseline Medication

	Control gr. n (%)	Intervention gr. n (%)
Betablockers	83 (86)	76 (76)

Calcium antagonist	6 (6)	18 (18)

Amiodarone	8 (8)	11 (11)

ACE inhibitors	67 (69)	69 (69)

Digoxin	8 (8)	12 (12)

Prolonged nitrates	7 (7)	4 (4)

Insulin	4 (4)	5 (5)

**Table 5 T5:** 6 MWT Baseline

	**Control gr. score**.	**Intervention gr. score**.
Distance meter (SD)	415 (118)	420 (112)

*Shortness of breath Pre-test (CI)	1.1 (0.7-1.3)	0.9 (0.5-1.3)

*Shortness of breath Post-test (CI)	3.2 (2.6-3.8)	2.8 (2.2-3.4)

*Exertion pre-test (CI)	2.1 (1.5-2.7)	1.7 (1.3-2.3)

*Exertion post-test (CI)	2.5 (1.8-3.1)	2.2 (1.5-2.8)

*BORG CR 10 Scale.

Mean values and 95% confidence interval

**Table 6 T6:** SF-36, QoL -cardiac version, SCA knowledge.

	Control gr. score, mean (SD)	Intervention gr. score, mean (SD)
PCS	43.4 (8.5)	41.9 (10.2)

MCS	46.7 (11.5)	47.4 (10.4)

Physical Function	69.8 (22.6)	69.7 (21.4)

Role Physical	39.1 (42.3)	36.6 (42.7)

Bodily Pain	71.2 (27.7)	71.2 (27.1)

General Health Perceptions	59.5 (19.2)	58.7 (21.9)

Vitality	53.5 (22.8)	55.6 (22.9)

Social Functioning	77.7 (24.9)	76.8 (25.9)

Role Emotional	56.3 (39.1)	51.0 (43.7)

Mental Health	69.3 (21.3)	72.5 (20.6)

QLI	26.5 (5.3)	26.3 (6.3)

HFSUBa	23.4 (5.7)	23.5 (6.9)

SOCSUBb	29.9 (6.4)	29.6 (7.1)

PSPSUBc	26.8 (9.4)	26.0 (8.2)

FAMSUBd	30.0 (5.1)	29.6 (8.7)

SCA knowledge	20.1 (3.1)	20 (3.7)

## Discussion

Demographic data and clinical variables are similar between the groups. The baseline characteristics are similar to other ICD rehabilitation populations regarding NYHA, LVEF, gender, type of device and indication [20,21]. The baseline measures of knowledge and skills needed to live with an ICD, SCA Knowledge score 20, are similar to the ICD rehabilitation population that originally tested the questionnaire, score 21 [20]. The population is also similar to other ICD populations regarding quality of life, with very similar scores in all subscales [47,48]. Perceived health measured by SF-36 is also similar to other findings as to the mental and emotional health, but with somewhat higher scores in physical function and pain [48].

Testing 6-MWT showed that this population might have a higher physical capacity (417 m) than other ICD populations (328 m, 383 m) [49,50], which can possibly be explained by a slightly higher LVEF and younger age.

This intervention is expensive from a rehabilitation perspective with 9 nurse consultations, 2 individual consultations with a physiotherapist and 2 weekly exercise training group sessions offered at the hospital. The planned economic analysis will reveal the cost-benefit ratio of this comprehensive rehabilitations programme. The set-up of this programme can be done in any cardiac rehabilitation setting after proper education of nurses and physiotherapists.

Study limitations include the fact that that selection bias may exist due to patients not being included if they were already included in a pharmaceutical trial. The control group might be contaminated by the information given during the project inclusion, suggesting that psycho-educational assistance and exercise training might be beneficial after ICD implantation. This information could lead to control patients seeking rehabilitation elsewhere if they believe it is effective. There is an expected drop-out rate at 20% which could influence the validity. Any difference between patients completing the intervention and those not completing (drop-outs) will be carefully discussed in evaluating the intervention, results and the suitability for implementation. The trial is designed with multiple statistical comparisons so results will be interpreted with caution.

In conclusion, whether a comprehensive rehabilitation programme improves quality of life and physical function have so far not been tested in larger prospective randomized controlled trials. The COPE-ICD trial is designed to test this hypothesis. The baseline data indicate a study population with heart failure, representative for ICD patients in general, similar to previous studies. This is the largest randomized trial in ICD patients to date, and will help determine the value of a comprehensive rehabilitation programme. Furthermore, the study's results will undoubtedly impact on rehabilitation practice and the control group in this study will provide valuable information on the current natural history of contemporary ICD patients. The first results will be published in 2011.

## Abbreviations

ICD: Implantable cardioverter defibrillator; COPE-ICD: Copenhagen Outpatient ProgrammE; METS: metabolic equivalent.
